### Intervention group

Patients assigned to the surgery group will be placed on the HUCSC waiting list and will undergo anesthetic risk assessment by the Anesthesiology Department. Antiaggregant or anticoagulant therapy will be perioperatively replaced with low-molecular weight heparin (LMWH).

Patients will be hospitalized the day before surgery and anesthetized in accordance with the preanesthetic assessment. The proposed treatment will consist in single-event multilevel surgery that includes the shoulder (tenotomy or pectoralis major and/or subscapularis lengthening), elbow (brachial biceps and anterior brachialis lengthening or musculocutaneous nerve hyponeurotization), forearm (pronator teres tenotomy or Scaglietti procedure [flexor-pronator mass release]), wrist (arthrodesis, tendon lengthening, tendon transfers, particularly superficialis-to-profundus tendon transfers), and hand (tendon lengthening, neurotomies of the motor branch of the ulnar nerve, and arthrodesis).

Hospital discharge is expected to be possible after drainages are removed and the patient has an adequate degree of analgesia. Patients will frequently undergo plaster cast immobilization and will be referred to the rehabilitation department for physical therapy after cast removal. Botulinum toxin will not be administered during the postoperative period.

### Control group

Patients in the control group will be treated with botulinum toxin in the rehabilitation department, receiving injections in upper limb spastic muscles at one session every 4 months.

### Data collection

Evaluations will be conducted by a specialist physician with >25 years’ experience at three time points: at baseline (t0) and at 6 months (t1) and 12 months (t2) post-intervention. Evaluations will be carried out in single sessions at Granada University School of Medicine except for the fMRI scan, which will be performed at the Mind, Brain, and Behavior Research Center of the University of Granada by technical staff at this center. (Fig 1).

Data will be collected on the following clinical and sociodemographic variables: age, sex, type of stroke, date of stroke, interval between stroke and treatment, gait capacity on the Functional Ambulation Classification (FAC) scale [40], upper limb lesion (functional or hygienic), cognitive status [41], family support, need for assistance (Barthel index) [42], and anesthetic risk (ASA) [43], classifying upper limb lesions as functional or hygienic hand and categorizing elbow, wrist, and hand deformities according to Keenan et al [33].

#### Functionality evaluation (main variable).

This evaluation will be performed at each time point (0, 6, and 12 months) using the following instruments:

1. Modified Ashworth spasticity scale [32], which measures the degree of spasticity from 0 to 5. Significant improvement at one or more of the five evaluated sites (elbow, forearm, wrist, thumb, fingers) will be considered a positive outcome.2. Hand function scale by House et al. [28], which considers nine functional grades.3. Zancolli hand classification [31].4. Fugl-Meyer scale for post-stroke recovery. It includes 33 items scored from 0 to 2 and a scale for shoulder-wrist and wrist-hand domains scored from 0 to 66 [29].5. VAS, which provides a subjective estimate of pain, using a line ranging from 0 “no pain” to 10 “worst pain imaginable” [34].

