### Aims, design, and setting

The primary aim of this study is to compare outcomes between surgery and a conventional approach with botulinum toxin in patients with post-stroke upper limb spasticity.

The secondary aims are:

To compare functional and hygienic changes (non-functional: esthetics, pain, and ease of care) in the spastic upper limb between surgery and botulinum toxin therapy using the House [28], Fugl Meyer [29], GAS [30], Zancolli [31], Modified Ashworth-Bohanon [32], Keenan [33] and the pain Visual Analog Scale (VAS) [34]To compare the impact on quality of life related to care and psychosocial risks of surgery *versus* botulinum toxin therapy in patients with post-stroke upper limb spasticity using SF 36 [35] and the Newcastle stroke-specific quality of life measure [36]To compare the effects on sleep quality (PSQI) [37], anxiety and depression (HADS) [38] of surgery *versus* botulinum toxin therapy in patients with post-stroke upper limb spasticity.To compare the effects on caregiver burden of surgery *versus* botulinum toxin therapy using the Zarit [39] and Caregiver Burden scales [7].To compare the effects on brain structure and function of surgery *versus* botulinum toxin therapy using fMRI.To perform a comparative cost-effectiveness analysis between patients with stroke sequelae treated with surgery *versus* botulinum toxin therapy.

The study will be a two-arm RCT in patients with post-stroke upper limb spasticity, randomly assigning participants to a Control group for botulinum toxin treatment or an Experimental Group for surgery (1:1 allocation ratio).

It will be conducted in Granada (940,974 inhabitants) and Jaén (620,242 inhabitants), two cities in in southern Spain, and will be led by Clínico San Cecilio University Hospital (CSCUH), Ciudad de Jaén University Hospital (CJUH), and the Surgery Department of Granada University.

The Project for this trial (Ref: PI20/01574) is funded by the *Instituto de Salud Carlos III* (ISCIII) and co-funded by the European Union. This research is part of the doctoral thesis of [name], developed under the Doctoral Program in Clinical Medicine and Public Health at the University of Granada (Spain).

A sample of 44 adults with post-stroke spastic upper limbs will be recruited for the study between 1^st^ January 2023 and 30^th^ June 2025.

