**Fig 1 pone.0322588.g001:**
[figure not shown]
Overview of the study.

Any patient who starts the study can abandon it at any time due to health, administrative or travel problems.

The sample size has been estimated for 5% type I error probability, 80% power, and a large effect size difference (0.8 standard deviations). Balanced one-way analysis of variance power calculation yielded K = 2, n = 16.71472, and f = 0.5. Accordingly, 34 patients (17 per group) are required with a minimum follow-up of 12 months. The sample size is set at 44 patients (22 patients in each group) to cover possible losses to the follow-up of 20%.

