### Data analysis

The Student’s t-test will be used for between-group comparisons of continuous variables, applying the Mann-Whitney U test when the distribution is non-normal. Repeated-measures regression analysis will be conducted for within-group comparisons between follow-up visits and baseline. McNemar’s Chi-square test or Fisher’s exact test will be used for between-group comparisons of discrete variables (e.g., Ashworth spasticity scale or Caregiver Burden Scale) and McNemar’s Chi-square test for within-group comparisons. Pearson’s correlation coefficient analysis will be applied to evaluate relationships between functional scores and the results of health, anxiety-depression, and sleep quality questionnaires. Multivariate linear regression will be performed to determine whether the functional improvement behaves as an independent variable with significant influence on aspects of psychosocial quality of life.

The fMRI results will be expressed descriptively and submitted to correlation analysis. The corrected BOLD response associated with the upper limb movement will be analyzed using a general linear model in SPM8, considering the aforementioned confounders and independent variables. The regression coefficients obtained for each patient will be analyzed by ANOVA to identify the brain regions that manifest effects associated with the variables of interest. Multiple comparison correction criteria will be applied for statistical decisions, resulting in an alpha error rate ≤0.05 throughout the trial.

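### No single primary endpoint is fixed: five unranked main instruments at two visits stand behind a sample size that spends the full 5% on one unnamed comparison

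*Protocol article*

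**What the plan says.** All references are to the Protocol article.

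- **Aims, design, and setting.** The primary aim is a comparison of outcomes between surgery and botulinum toxin, with no scale and no visit. The first secondary aim is "To compare functional and hygienic changes (non-functional: esthetics, pain, and ease of care) in the spastic upper limb", using House, Fugl-Meyer, GAS, Zancolli, Ashworth, Keenan and the pain VAS. Pain is classed there as non-functional.
- **Functionality evaluation.** The heading is "Functionality evaluation (main variable". It lists Modified Ashworth, House, Zancolli, Fugl-Meyer and the pain VAS, each at 0, 6 and 12 months. None is ranked first and neither follow-up visit is preferred. Ashworth counts as positive on improvement at any one of five sites.
- **Table 2.** Seven functional and hygienic scales at 6 and 12 months form one outcome row.
- **Participants, sample-size paragraph.** "The sample size has been estimated for 5% type I error probability, 80% power", and "a large effect size difference (0.8 standard deviations". The calculation is "Balanced one-way analysis of variance power calculation yielded K = 2, n = 16.71472, and f = 0.5", from which "34 patients (17 per group) are required with a minimum follow-up of 12 months". The outcome being sized is not named. Allowing for 20% loss gives 44 patients.
- **Data analysis.** The second paragraph, on fMRI, ends by promising a multiple-comparison correction, "resulting in an alpha error rate ≤0.05 throughout the trial". The paragraph on the clinical scales mentions no correction.

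**The concern.** The same functional scales are secondary in one section and main in another, and pain changes category between the two. A reader cannot tell which result decides the trial. The sample size assumes that exactly one test does, at the full 5%, while the main variable supplies five tests at one visit or ten over two.

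Either the error rate is shared among those tests, and the planned power does not apply to any one of them, or it is not shared, and surgery could be declared superior on whichever test is significant. The Discussion states the expectation that surgery will improve every study parameter, so almost any significant scale could be read as confirming it.

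**Working it through.** **Inputs.** Alpha 5%, power 80%, K = 2, f = 0.5, 17 evaluable per group, 20% loss (Participants). Five instruments and two follow-up visits (Functionality evaluation). Bonferroni and the correlations between tests are assumptions; the document names no correction method and gives no correlations.

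**Step 1: reproduce the stated size.** For two equal groups, f = d/2, so f = 0.5 means d = 1.0 SD. Power is P[F(1, 2n−2; λ) > critical F], with λ = 2n·f². Solving for 80% at alpha 0.05 gives n = 16.71472, the printed figure, which rounds up to 17. Then 17/0.80 = 21.25, rounded up to 22 per group, 44 in all. At n = 17, λ = 34 × 0.25 = 8.5 and power is 80.7%. The figure therefore reproduces with one test at the full 5%, equivalent to a two-sided t-test, and nothing reserved for multiplicity.

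**Step 2: if the correction covers the main scales.** Bonferroni, 17 per group, d = 1.0 SD:

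| Main tests | Alpha per test | Power per test |
|---|---|---|
| 1 | 0.05 | 80.7% |
| 5 (12 months only) | 0.05/5 = 0.01 | 57.5% |
| 10 (both visits) | 0.05/10 = 0.005 | 47.2% |

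**Step 3: if it does not.** For m independent tests, each at 5%, the chance of at least one false positive is 1 − 0.95^m: 1 − 0.95^5 = 22.6% and 1 − 0.95^10 = 40.1%. Simulation with equally correlated normal test statistics gives:

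| Correlation | 5 tests | 10 tests |
|---|---|---|
| 0.5 | 18.3% | 28.7% |
| 0.7 | 14.9% | 21.3% |
| 0.9 | 10.1% | 12.7% |

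**Step 4: one named endpoint.** At 5% and 17 per group, power is 80.7% for d = 1.0. For the 0.8 SD given in words, f = 0.4, λ = 34 × 0.16 = 5.44 and power is 61.9%. That shortfall comes from the mismatch between 0.8 SD and f = 0.5. It is a separate issue and is not caused by multiplicity.

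**The case against.** A reader might infer that the document contradicts itself outright: a trial-wide 5%, many main tests, and 80% power from one uncorrected test. The text does not establish this. The alpha sentence follows the sentence on identifying brain regions, and the imaging section has its own correction (random field theory). Its wording is trial-wide, but an imaging-only reading is plausible. On that reading nothing conflicts with the sample size, and what remains is that the main scales have no stated error control.

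A reader might also take 57.5% or 47.2% as the power of the trial. They are powers for one given scale. If a win on any scale counts and every scale carries a 1.0 SD effect (an assumption), simulated power for at least one win, with Bonferroni over ten tests and 17 per group, is about 90%, 82% and 67% at correlations of 0.5, 0.7 and 0.9. Effects on only some scales would lower these figures. Bonferroni is also conservative for correlated scales.

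Ten tests is the upper count for five instruments at two visits. The 12-month minimum follow-up in the sample-size paragraph hints at 12 months as the key visit, without designating it; that reading gives five. The Data analysis section treats Ashworth as discrete and Zancolli is a classification, so t-test power only approximates theirs.

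Finally, an analysis plan that is not shown could hold the correction method. That point stands for the method. The aims, the main variable and the alpha behind the sample size are stated in this document, and here they do not line up.

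**Conclusion.** The point holds in this form: no primary instrument or visit is fixed, the functional scales are both secondary and main, and the sample size fits one unnamed test at 5%. What follows depends on how the alpha sentence is read.

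- **Covers the clinical scales:** the stated 80% does not hold for any given scale (57.5% or 47.2% under Bonferroni at 1.0 SD). Power to win on at least one scale may be higher.
- **Covers imaging only:** the chance of at least one false positive among the main tests is 23% to 40% if independent, and about 10% to 29% over the assumed correlations of 0.5 to 0.9.

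On either reading the document leaves open which result carries the main claim. It does not support the stronger statement that its passages on alpha and power are necessarily incompatible.

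**What to change.** Name one primary instrument at one visit, tested at two-sided 5%. Choose it without sight of data by arm, and date the choice in the protocol and registry. Recruitment began in January 2023, so the record should state that no data by arm informed the choice. Change in the Fugl-Meyer upper-limb total at 12 months is one example, since the sample-size paragraph already requires 12 months of follow-up; the choice of scale belongs to the trial team.

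Make the other four instruments and the 6-month visit secondary with a Holm correction. Align the aims, the Functionality evaluation heading (including where pain belongs) and Table 2. State in Data analysis whether the correction covers the clinical scales.

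The cost is a change of protocol and registry wording, and the other scales can no longer carry the main claim. Naming the endpoint adds no patients or visits, but it does not repair the effect-size mismatch: restate separately whether the design effect is 0.8 or 1.0 SD, because the stated N reaches 80% only at the latter.

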#### Evaluation of hygienic or nonfunctional achievements (secondary variable) and caregiver burden.

This evaluation will be performed at each time point (0, 6, and 12 months) using the following instruments:

“GAS score” [30], a 5-point scale score for hygiene, esthetics, and pain domains.Caregiver Burden Scale [7], which rates the degree of difficulty of caregivers in four basic activities (nail-cutting, palm washing, axilla washing, upper limb dressing) using a 5-point “Likert” scale.Zarit Caregiver Burden questionnaire [39].

#### Quality of life evaluation.

This evaluation will be performed at each time point (0, 6, and 12 months) using a generic questionnaire (Spanish-validated version of SF-36 [35]) and a quality-of-life-specific questionary (New Castle Stroke-Specific Quality of Life measure [36]).

#### Evaluation of sleep quality, anxiety, and depression.

This evaluation will be performed at each time point (0, 6, and 12 months) using the following instruments:

Pittsburgh Sleep Quality Index (PSQI) questionnaire (Spanish version validated by a member of the present research team [37]), which includes 19 self-evaluated questions covering seven domains: quality, latency, duration, habitual efficiency, discomfort, use of sleeping medication, and day-time dysfunction. Item and domain scores range from 0 to 3 (higher score = worse quality).

Hospital Anxiety and Depression Scale (HADS) questionnaire (validated Spanish version [38]), which includes 14 items with scores from 0 to 3 (higher score = more severe symptom).

#### Evaluation of brain activity, structure, and function.

This evaluation will be performed at each time point (0, 6, and 12 months) by using the fMRI at rest and with repeated attempts of patients at the flexion-extension of elbow, wrist, and fingers. Anatomical and functional volumes will be obtained from MRI and fMRI images using a 3T Siemens Prisma fMRI. A three-dimensional volume will be acquired in each patient by using a T1-weighted 3D-turbo-gradient-echo (3D-TFE) sequence in sagittal orientation, with 1x1x1 mm resolution (160 slides, FOV = 240 mm2, 256x256x160 matrix, 8 s repetition time, 4 ms echo time, 8º flip angle, and 191 Hz/pixel band width). Each functional examination will include 180 volumes with a T2*-weighted echoplanar imaging (EPI) cranium sequence using the following parameters: repetition time = 2.0 s, echo time = 30 ms, flip angle = 70º, 33 slices with 3-mm width and 1-mm gap, 3 mm in-plane resolution). MRI images will be analyzed using SPM (version 8, http://www.fil.ion.ucl.ac.uk/spm/software/spm8/) and FSL (version 5.0, http://fsl.fmrib.ox.ac.uk/fsl/fslwiki/) open software packages. In anatomical images, the DARTEL algorithm (Diffeomorphic anatomical registration through exponentiated Lie algebra) will be used to measure grey matter and white matter volumes. Subcortical structures (hippocampus, basal ganglia, amygdala, nucleus accumbens, and brainstem) will be segmented using the FIRST algorithm implemented in FSL, which allows the volume and shape of these structures to be determined. The shape measurement will use the medial distance from each point of the structure surface to its medial axis. The general linear model implemented in the SPM8 and FSL packages will be used for the statistical analysis. The random field theory (RFT) correction will be applied to address the problem of multiple comparisons, and SPM12 (http://www.fil.ion.ucl.ac.uk/spm/software/spm12/) will be used for fMRI image processing and analysis.

#### Evaluation of health costs.

Health resources consumed by participants will be calculated in accordance with an economic model developed to compare surgical treatment with botulinum toxin alone in the Spanish setting. Clinical records will be reviewed to gather data on medication, specialist visits, primary health care consultations, and health transportation. Prices in the Pharmaceutical School Council Catalog will be applied to medications. Information in the Spanish eSalud health cost database will be used to generate a unitary cost for primary and specialized care consultations, emergencies (hospital and primary care), and health transportation. Hospitalization costs will be based on mean values published by the Ministry of Health, Social Policy, and Equality for the corresponding diagnostic groups. Account will also be taken of the need for occupational therapy. Costs of the main caregiver and secondary caregivers will be based on the hours they devote to care activities, applying the market hourly rate for similar services. In addition, a cost-utility analysis will be performed based on patient-reported quality-of-life results.

Outcome measures are summarized in Table 2.

**Table 2 pone.0322588.t002:** Summary of outcome measures. GAS: Goal Attainment Scale; HADS: Hospital Anxiety and Depression Scale; MRI: Magnetic Resonance Imaging; PSQI: Pittsburgh Sleep Quality Index; SF-36: 36-item Short Form Survey.

Outcomes	Time point	Measurement definition
Change in functional and hygienic status of the affected upper limb	6 and 12 months	Measured using House, Keenan, Zancolli, Fugl Meyer, GAS, Asworth and VAS scales
Change in quality of life	6 and 12 months	Measured using SF 36 and New Castle Stroke-Specific quality of life scale
Changes in sleep quality	6 and 12 months	Measured using the PSQI
Changes in anxiety and depression	6 and 12 months	Measured using HADS score
Changes in caregiver burden	6 and 12 months	Measured using Carer Burden and Zarit scales
Changes in brain structure	6 and 12 months	Measured using MRI
Changes in brain function	6 and 12 months	Measured using fMRI
Treatment costs	12 months	Using model to simulate costs and quality-adjusted life years. Unit costs from published Spanish sources

[name] and [name] will be the data monitoring committee; who will maintain continuous contact with patients to reduce the risk of dropout and will ensure that no patient misses any assessment during the follow-up period, and will be responsible for reporting any adverse event related or not to the treatment applied, as well as making the decision to terminate the trial. Auditing trial conduct will be carried out monthly.

Access to the final trial dataset will be allowed to principal investigator, data monitoring committee, and responsible biostatistician.

### Data analysis

The Student’s t-test will be used for between-group comparisons of continuous variables, applying the Mann-Whitney U test when the distribution is non-normal. Repeated-measures regression analysis will be conducted for within-group comparisons between follow-up visits and baseline. McNemar’s Chi-square test or Fisher’s exact test will be used for between-group comparisons of discrete variables (e.g., Ashworth spasticity scale or Caregiver Burden Scale) and McNemar’s Chi-square test for within-group comparisons. Pearson’s correlation coefficient analysis will be applied to evaluate relationships between functional scores and the results of health, anxiety-depression, and sleep quality questionnaires. Multivariate linear regression will be performed to determine whether the functional improvement behaves as an independent variable with significant influence on aspects of psychosocial quality of life.

The fMRI results will be expressed descriptively and submitted to correlation analysis. The corrected BOLD response associated with the upper limb movement will be analyzed using a general linear model in SPM8, considering the aforementioned confounders and independent variables. The regression coefficients obtained for each patient will be analyzed by ANOVA to identify the brain regions that manifest effects associated with the variables of interest. Multiple comparison correction criteria will be applied for statistical decisions, resulting in an alpha error rate ≤0.05 throughout the trial.

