**Methods:**

A two-arm (surgical treatment [n = 22] *vs*. botulinum toxin [n = 22]) randomized clinical trial (RCT) will be performed to compare the efficacy of surgery with that of botulinum toxin treatment in patients with post-stroke upper limb spasticity. Data will be collected at baseline and at 6 and 12 months of follow-up on functionality, hygienic status, quality of life, sleep quality, anxiety/depression levels, and functional magnetic resonance imaging (fMRI)-measured brain activity. Healthcare and care costs will be compared between the groups.

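### Read literally, the general switch to Mann-Whitney reaches the between-group cost comparison, where the economic aims need a difference in mean cost; costs should be exempted

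*Protocol article*

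**What the plan says.** Three parts of the protocol article bear on this.

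- **The test rule (Data analysis).** "The Student’s t-test will be used for between-group comparisons of continuous variables, applying the Mann-Whitney U test when the distribution is non-normal". Discrete scales and fMRI get their own methods in the same section. Costs and quality-adjusted life years (QALYs) are not mentioned there, either under the rule or as an exception to it.
- **The comparison (abstract, Methods; Aims, design, and setting).** "Healthcare and care costs will be compared between the groups", and one secondary aim is "To perform a comparative cost-effectiveness analysis between patients with stroke sequelae treated with surgery *versus* botulinum toxin therapy".
- **How costs arise (Evaluation of health costs; Table 2).** "Health resources consumed by participants will be calculated in accordance with an economic model developed to compare surgical treatment with botulinum toxin alone". Inputs are clinical records, published unit prices, hospital stays priced at published averages for diagnostic groups, and caregiver hours. Table 2 defines the 12-month cost outcome as "Using model to simulate costs and quality-adjusted life years. Unit costs from published Spanish sources". The section adds: "In addition, a cost-utility analysis will be performed based on patient-reported quality-of-life results".

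**The concern.** An incremental cost, or a cost per QALY, is built from arithmetic means: mean cost per patient in one arm minus the mean in the other. Mann-Whitney does not test that difference. Its null hypothesis is that the two distributions are the same, and it responds to whether a patient from one arm tends to rank above a patient from the other. For skewed data with different spread in the two arms, the two questions can have different answers.

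Per-patient costs that include admissions and caregiver hours are a natural candidate for the non-normal branch. The article also gives a reason why shapes might differ: every operated patient is admitted (Intervention group), and admissions are priced at averages. This adds a nearly constant amount to one arm and lowers that arm's relative spread.

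At stake is a reported p-value for a cost difference that disagrees with the incremental cost in the economic analysis. It could be significant when mean costs are equal, or miss a difference in means that a few expensive patients produce.

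**Working it through.** **Sample sizes.** The plan states no figure for the cost comparison, so the only figure to reproduce is the sample size, which supplies the arm sizes. For a balanced one-way ANOVA with k = 2, power is the upper tail of a noncentral F with 1 and 2(n − 1) degrees of freedom and noncentrality λ = 2·n·f². Solving for 80% power at f = 0.5 gives n = 16.7147, which matches "Balanced one-way analysis of variance power calculation yielded K = 2, n = 16.71472, and f = 0.5". Power at 17 per arm is 80.7%, and 17/(1 − 0.20) = 21.25, rounded up to 22. (In two equal groups 0.8 SD corresponds to f = 0.4. That is a separate matter and is not used here.) The check uses 17 and 22 per arm.

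**Assumptions, none from the article.** Lognormal costs; the coefficients of variation (CV); and, for the switch, a Shapiro-Wilk p-value below 0.05 in either arm. The article names no normality test.

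**Why ranks and means part company.** For lognormal cost with mean m, σ² = ln(1 + CV²) and the log-scale mean is ln m − σ²/2. With equal means, the chance that a patient from the low-CV arm A costs more than one from arm B is Φ[(σ_B² − σ_A²)/2 ÷ √(σ_A² + σ_B²)].

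For CV 0.3 versus 1.0: σ_A² = ln 1.09 = 0.086 and σ_B² = ln 2 = 0.693. Then (0.693 − 0.086)/2 = 0.303, √0.779 = 0.883, and Φ(0.344) = 0.63. The median ratio is e^0.303 = 1.35. So mean costs are equal, yet arm A ranks higher 63% of the time. Mann-Whitney picks this up.

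**Rejection at two-sided 5% with equal mean costs (20,000 trials per row):**

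| CV pair | Mann-Whitney, 17 | Welch, 17 | Mann-Whitney, 22 | Welch, 22 |
|---|---|---|---|---|
| 0.5 / 0.5 | 4.7% | 4.6% | 4.7% | 4.7% |
| 1.0 / 1.0 | 5.0% | 3.7% | 4.7% | 3.9% |
| 0.3 / 0.6 | 11.3% | 6.1% | 13.1% | 5.7% |
| 0.5 / 1.0 | 16.4% | 6.9% | 20.2% | 7.1% |
| 0.3 / 1.0 | 27.8% | 9.8% | 34.4% | 8.9% |
| 0.5 / 1.5 | 35.2% | 11.2% | 43.8% | 10.8% |
| 0.3 / 1.5 | 47.2% | 14.2% | 57.1% | 13.1% |

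The two-stage rule (first 4,000 trials of each row) follows Mann-Whitney closely. At 22 per arm it rejects 12.9%, 21.0%, 33.4% and 56.8% for 0.3/0.6, 0.5/1.0, 0.3/1.0 and 0.3/1.5. In the unequal-CV rows it switches to Mann-Whitney in 61% to 99% of trials.

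**A structure closer to the article's costing.** Let each arm's cost be a fixed share of its mean plus lognormal care cost, with the same CV of the variable part (0.5 to 1.0) in both arms and equal total means. The total CV is (1 − fixed share) × CV, so a 50% share at CV 1.0 gives 0.5.

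- Fixed share 10% in control and 20% to 30% in surgery: Mann-Whitney rejects 5% to 9%.
- Control 10%, surgery 40% to 50%: 7% to 22%.
- Control 0%, surgery 50%, CV 1.0: the two-stage rule rejects 21% at 17 per arm and 26% at 22.
- Surgery 60%, CV 1.0, control 0% to 10%: 23% to 32%.

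Welch stays between 4% and 8% over these settings.

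**The reverse case.** With equal medians and mean costs 35% and 73% apart (CV 0.3 versus 1.0 and 0.3 versus 1.5, 22 per arm), Mann-Whitney rejects 6.8% and 7.5%, and Welch 13.5% and 18.5%. Neither has much power, but Mann-Whitney is almost blind to the difference.

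**The case against.** The strongest reply is that the Data analysis section never mentions costs. Costs have their own section, and Table 2 assigns them to an economic model that simulates costs and QALYs. A journal article may properly leave the inference for such a model to a fuller document. This stands in part: it is an inference that the rule reaches costs, and the absence of a health-economic method is not itself a fault. What remains is that a general rule is stated, other outcome types are carved out of it and costs are not, while a between-group comparison of costs is promised.

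A reader might go further and infer that the plan will test costs with Mann-Whitney, so that the economic conclusion rests on the wrong hypothesis. The documents do not support that. No section says costs will be tested on ranks, and neither a cost-effectiveness ratio nor a cost per QALY uses a Mann-Whitney p-value. At most, an accompanying p-value could disagree with the incremental cost.

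A reader might also take the highest rejection rates as what to expect. They need a fivefold ratio of CVs. Both arms share variable components such as consultations, transport and caregiver hours, and with equal shapes the error stays near 5%.

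Finally, the alternative is not clean. Welch rejects about 6% to 14% in the unequal-CV lognormal settings, and a simple percentile bootstrap rejected about 9% to 17% for CV 0.3 versus 0.8 to 1.5. Studentised or bias-corrected bootstraps and a generalised linear model were not tried. That stands, although these rates are still well below Mann-Whitney's in the same settings.

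**Conclusion.** The point holds as a literal reading of an unrestricted rule. Unless costs are exempted, the rule sends non-normal costs to a test that does not address the mean cost difference the economic aims require, and its p-value could contradict the modelled incremental cost.

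The harm is conditional on non-normal costs and on different shapes in the two arms. Under lognormal costs with equal means at 17 to 22 per arm, false rejection is about 5% with equal shapes and about 11% to 57% for the assumed CV pairs from 0.3 versus 0.6 to 0.3 versus 1.5. It is roughly 5% to 26% when a fixed surgical cost of up to about half the arm's mean is added to otherwise similar variable costs. The article gives no cost distribution, so these figures show a mechanism and a range, not a forecast. It is a minor correction to a secondary aim and leaves the clinical comparisons untouched.

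**What to change.** Add to the Data analysis section that per-patient costs are exempt from the normality-based switch. The arms are compared on the difference in arithmetic mean cost with a 95% interval (Welch or non-parametric bootstrap), whatever the distribution, and medians are shown descriptively only. State that this difference is the one used in the economic model under Evaluation of health costs, so that the reported comparison and the incremental cost agree.

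The cost is one sentence and a short piece of analysis code, with no extra patients or data. Intervals for mean cost will be wide at 17 to 22 per arm, and mean-based error rates remain somewhat above 5% under strong skew. The result should therefore be presented mainly as an estimate with its uncertainty.
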